## Abstract

**Background:**

Head impacts are common in contact sports such as boxing and occur at times of elevated core body and brain temperatures induced by the exercise. Following impact, elevated brain temperature may lead to the development of exacerbated brain injury that can be monitored by blood biomarkers. Blood-brain biomarkers S100B and glial fibrillary acidic protein (GFAP) reflect glial injury; neurofilament light (NFL), axonal injury; and Neuron-Specific Enolase (NSE) and Tubulin-associated unit (tau), neuronal injury. Time to peak levels post injury for these biomarkers varies. Levels of S100B l peak early post injury, while NSE, GFAP, and tau are regarded as subacute markers, and NFL shows prolonged increases. We attempt to cover a large spectrum of first week postfight alterations in blood-brain biomarkers and their response to head-neck cooling.

**Objective:**

We hypothesized that acute head-and-neck cooling, recently shown to shorten return-to-play in concussed ice hockey players, applied acutely following a boxing bout, is associated with an attenuated concentration of blood biomarkers and improved symptom rating.

**Methods:**

The trial is academically driven and funded by external and hospital research funds. Young, healthy elite boxers aged ≥18 years are recruited. Before, and immediately after a competitive boxing bout consisting of 2 or 3 rounds of 2 minutes each, blood samples are drawn. Boxers are randomized to intervention or control management by 1:1 allocation before baseline testing. After the initial postfight blood sample is drawn and symptom rating using the Sports Concussion Assessment Tool-5 (SCAT-5) has been collected, the boxers receive either acute selective head-and-neck cooling for 45 minutes or routine postfight management. The number of head impacts is counted in all boxers on match video recordings. In both groups, blood samples are drawn 45 minutes after the initial postbout blood sample, as well as 3 and 6 days post fight. At all blood sampling time points, the number of symptoms (NOS) and symptom severity score (SSS) are assessed using the symptom rating part of the SCAT-5. The primary endpoint is the difference in biomarker levels (GFAP, NFL, tau, UCH-L1, neuronal-specific enolase) immediately post fight and preintervention, to those obtained at 6 days post fight. The postfight SCAT-5 NOS and SSS are secondary endpoints.

**Results:**

Recruitment started in November 2021 and is ongoing. So far, 41 boxers have been included: 20 controls and 21 cooled. Data collection started in October 2024 following the completion of blood sample analysis. We expect to recruit more boxers before the middle of 2025, but challenges with recruitment may limit this.

**Conclusions:**

There is no treatment available for boxing-induced brain injury. Biomarkers are surrogate yet objective markers of brain injury, and the head-and-neck cooling treatment may attenuate the concentration of brain injury–related biomarkers as well as reduce symptoms induced by head impacts attained during a boxing fight.

**Trial Registration:**

ClinicalTrials.gov NCT06386484; https://clinicaltrials.gov/study/NCT06386484

**International Registered Report Identifier (IRRID):**

DERR1-10.2196/68954

## Introduction

### Background

Trauma to the head is common in many contact sports, including boxing [1]. If the trauma to the head, or the body with energy transmitted to the head, is sufficient to induce a range of clinical symptoms and signs that may or may not involve loss of consciousness, a sport-related concussion (SRC) has occurred [2]. In boxing, participants both receive and deliver, on average, 32-40 blows to the head during a typical bout [3]. Those blows are referred to as repetitive head impacts (RHI) [4,5]. RHI differs from the definition of SRC by the absence of the acute symptoms typically observed following an SRC. However, similar to after several SRCs cumulative effects of RHI include early-phase changes in brain function and increased risk for neurodegenerative disorders at long-term. Neuropathological consequences of RHIs in boxing have been comprehensively investigated in previous studies, illustrating structural alterations to the brain [2,6]. More specifically, RHI may lead to cognitive impairment, mood disorders, and motor control problems [7-9].

Several studies have shown that retired athletes who have sustained multiple RHI and SRCs during their career may develop chronic traumatic encephalopathy (CTE), a progressive neurodegenerative disease associated with memory loss, depression, personality changes, and dementia [1,8,10-13]. At present, CTE can only be diagnosed post mortem where key findings include irregular aggregation of phosphorylated tau protein at the depths of cortical sulci [8].

In sports, strenuous exercise leads to elevated core body and brain temperature [14], which may exacerbate the brain injury induced by head impacts. Recently, we showed that selective head-and-neck cooling for 45 minutes, aiming to rapidly normalize the elevated brain temperature, applied acutely post SRC in elite ice hockey players, resulted in earlier return-to-play and a smaller proportion of players with prolonged symptoms following the SRC [15]. However, there is a lack of objective outcome measures for assessing the effects of head-and-neck cooling in athletes.

There is a growing body of literature on the use of biomarkers of brain injury in athletes. In Olympic boxers, levels of cerebrospinal fluid biomarkers such as S100 calcium-binding protein (S100B), Tubulin-associated unit (Tau), Neurofilament light (NFL), and Glial fibrillary acid protein (GFAP) were collected at baseline, 1-6 days post fight, and 14 days after RHI attained in a boxing bout [16,17]. In addition, the biomarkers showed both acute and cumulative effects of the impacts, with a lack of normalization of NFL and GFAP after the rest period, which may indicate an ongoing injury process [16,17]. In addition, inflammatory biomarkers such as tumor necrosis factor-alpha, interleukin 6, and muscle injury biomarkers (alanine aminotransferase and aspartate aminotransferase), and creatinine increased in male elite boxers following a fight [18].

When boxing and mixed martial arts (MMA) were compared, retired boxers had higher plasma GFAP levels, and active boxers had higher plasma NFL than MMA fighters [19]. In addition, serum NFL levels were elevated both at 7-10 days post bout and after 3 months of rest in boxers compared to controls. This study also observed a significant increase in NFL at 7-10 days post bout comparing levels obtained after a high number of head impacts (more than 15 hits to the head or experienced grogginess during or after bout) to those obtained after fewer head impacts (fewer than 15 head hits) [20]. These studies indicate that selected biomarkers may remain elevated during the first postinjury week. In this randomized trial, we hypothesized that biomarkers could serve as an objective marker for the efficacy of selective head-and-neck cooling on attenuating brain injury in elite boxers, assessed by blood biomarkers immediately before and during the first 6 days after a competitive boxing fight.

### Objectives

#### Research Hypothesis

The research hypothesis was that acute and selective head-and-neck cooling immediately after a boxing bout attenuated brain injury as evident by a reduced concentration of brain injury-related biomarker levels during the first postfight week.

#### Study Objectives

The primary objective was to determine whether selective head-and-neck cooling attenuates the concentration of brain injury biomarkers.

The secondary objectives were as follows:

To determine whether selective head-and-neck cooling improves symptom rating using the Sports Concussion Assessment Tool-5 (SCAT-5).To determine whether any biomarker increase post fight, compared to baseline levels, is associated with the number of head impacts.To determine any adverse event associated with the head-and-neck cooling.

## Methods

### Participants, Interventions, and Outcomes

#### Study Setting

The study will take place predominantly in the southern parts of Sweden due to logistical reasons, aiming for the feasibility of follow-up with biomarkers at distinct postfight time points. Blood samples will be collected at the site of the competitive boxing tournament or the local boxing clubs and transferred to the biobank at Lund University Hospital. All data will be collected in Sweden. The trial is academically driven by local funding. The trial will be conducted at Lund University, Lund, Sweden.

#### Trial Design

The head-and-neck Cooling of Brain temperature In BOXing (COBIBOX) trial is designed as a randomized, controlled, open, single-center superiority trial with 2 parallel groups and a primary endpoint of biomarker changes during the first 6 postfight days. Clinical secondary outcome assessments of a number of symptoms (NOS) and symptom severity score (SSS) using the symptom rating part of the SCAT-5 is performed during the initial 6 postinjury days. Randomization will be performed in blocks with 1:1 allocation.

#### Eligibility Criteria

Eligibility criteria are listed in Textbox 1.

Inclusion and exclusion criteria.
**Inclusion criteria**
Male and female elite boxers <40 years old and ≥18 years old.Cleared for participation by the medical staff of the Swedish Boxing Association before the boxing bout.Informed consent by each participant before the competitive event.
**Exclusion criteria**
>40 years old or <18 years old.Participation in competitive fights, match-sparring, or any training causing additional head impacts during the 6-day postfight follow-up period after being included in the study.History of autoimmune neurological diseases or a neurodegenerative disorder.History of previous traumatic brain injury resulting in an intracranial hemorrhage.

#### Procedures and Measurements

All boxing clubs are thoroughly informed of the protocol before study initiation and before each tournament. Boxers between the ages of 18 and 40 years are included. At each tournament, allocation to the treatment takes place on the first morning, and the boxers are randomized 1:1 by a randomly drawn paper slip with a sign that the boxer will receive either selective head-and-neck cooling or routine postfight medical surveillance by an on-site physician. The selective head-and-neck cooling is to be initiated within 10 minutes post fight with a duration of a minimum of 45 minutes. After the boxer completes the fight (Figures 1 and 2), he or she follows the researcher to the cooling station and continues the head-and-neck cooling protocol. In some boxing events, a boxer may participate in two bouts if they win their first bout (Figure 2). The next day, during the finals, they will undergo the same protocol as on their first day, including SCAT-5 assessments and blood sample collection [21]. As mentioned in Figure 2, the start of intervention or return to play protocol starts after their last fight.

Participants will be randomly allocated to either the control or intervention group, involving selective head-and-neck cooling. Baseline SCAT-5 and blood samples will be collected. Subsequently, postfight SCAT-5 and blood samples will be collected for both groups. In addition, the intervention group will undergo selective head-and-neck cooling for 45 minutes. Following this, both the control and intervention groups will follow the same protocol, undergoing SCAT-5 and blood sample collection at 45 minutes post fight, as well as on day 3 and day 6 for follow-up (Figure 1).

The selective head-and-neck cooling takes place after the last boxing bout (dark-colored boxes). For a boxer who fights bout 2/2, new baseline SCAT 5 and blood samples will be collected, shown as baseline 2.0 in Figure 2.

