**Figure 3 figure3:**
[figure not shown]
(A) The PolarCap unit is a powerful mobile cooling system. (B) The Polar Coolant is transported through the silicone head cap. (C) To insulate against the cold, a neoprene cover is applied on top of the cap.

Blood samples are collected at the following time points for all participants: the morning of the first boxing fight on day 1 (baseline, at rest), immediately after the fight, 45 minutes after the fight, and after 3 and 6 days in all boxers. The blood samples obtained at 3 and 6 days post fight will be drawn by a study nurse or a researcher ([name]) at the participants’ boxing club. The samples are transported to the hospital in a mobile refrigerator to maintain a temperature of 5-8 °C. Thereafter the serum samples are centrifuged at 3000 rpm, at 4 °C for 10 minutes, after which 800-1200 µL is transferred using a pipet to 2-mL tubes and stored at –80 °C.

At each time point for blood sample collection, boxers are also administered the SCAT-5 questionnaire, which is a self-report questionnaire with information on 22 different symptoms, each with a severity grading of 0-6, where 0 indicates no symptoms and 5-6 indicates severe symptoms. The maximum total score is 132. All boxing bouts are video-recorded for later analysis. The total hits per bout, strikes to the head, strikes to the body, and visible evidence of neurological disturbance (loss of consciousness, impaired balance or coordination, vacant expression, etc) will be assessed. After completion of the study, the boxers will be interviewed by phone to answer questions about their previous boxing, knock-out, and concussion history. The timeline for enrollment intervention and assessments across the study is visualized in Table 1 (SPIRIT [Standard Protocol Items: Recommendations for Interventional Trials] checklist in Multimedia Appendix 1).

**Table 1 table1:** Timeline of enrollment, intervention, and assessment during the study period.

Procedures		Study period				Post allocation						Close-out
		Enrollment	Preallocation	Allocation								
Time point		–t_1_	Baseline	0	Post fight		45 min post fight	Day 3	Day 6	1 week post fight		
**Enrollment**		✓										
	Eligibility screen	✓										
	Informed consent	✓										
	Basic medical examination	✓										
	Allocation			✓								

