### Data Collection

The SCAT-5 form will be filled out at the time of biomarker analysis and used as a secondary endpoint of the study. The boxing bouts take place either in events consisting of single bouts for each boxer or in tournaments where 2 bouts are possible (semifinal and final). For boxers participating in two bouts at the same event, the baseline, postfight, and 45-minute postfight scores and biomarker tests will be retaken. Values related to the second fight will be considered in the analysis. The analysis of symptom severity scores obtained by SCAT-5 at the set timeline will facilitate the interpretation of outcomes between the boxers independent of their previous boxing history after the completed 6-day follow-up. Boxing history will be obtained by phone call interview at the 6-day follow-up or on-site. The follow-up for days 3 and 6 will be organized by the local clubs before the first postmatch training session, or at the study hospital.

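### The 45-minute sample has two different time origins, and under neither does it fall after cooling has ended, although the protocol says it follows cooling

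*Protocol article*

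**What the plan says.** **Time origin.** The Abstract (Methods) counts from the initial post-fight draw: "In both groups, blood samples are drawn 45 minutes after the initial postbout blood sample". Three places in the body count from the fight. Procedures and Measurements has both groups "undergoing SCAT-5 and blood sample collection at 45 minutes post fight". The sampling list after Figure 3 reads "immediately after the fight, 45 minutes after the fight, and after 3 and 6 days in all boxers", and Table 1 labels its column the same way. Data Collection, on boxers with two bouts, says that "the baseline, postfight, and 45-minute postfight scores and biomarker tests will be retaken".

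**Cooling window.** Procedures and Measurements gives a latest start and a minimum duration: "The selective head-and-neck cooling is to be initiated within 10 minutes post fight with a duration of a minimum of 45 minutes". Two paragraphs on, the duration appears without a minimum: "the intervention group will undergo selective head-and-neck cooling for 45 minutes".

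**Order.** In the Abstract, cooling or routine management comes "After the initial postfight blood sample is drawn and symptom rating using the Sports Concussion Assessment Tool-5 (SCAT-5) has been collected". Procedures and Measurements then describes the 45-minute sample and SCAT-5 as coming after the cooling step, under the same protocol in both groups.

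**The concern.** Staff cannot follow both clocks, and the order given in Procedures and Measurements cannot be met for any boxer whose cooling starts after minute 0. On site there are two ways out: assess the cooled boxer while the cap is still on, or wait until cooling ends. Only the cooled arm has a reason to wait, and no passage delays controls to match.

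Two comparisons are exposed.

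- **Biomarkers.** This is the only draw between the immediate post-fight sample and day 3. The Discussion says S100B peaks within hours and lists it among the markers that may matter most. For a marker that is changing quickly, a time shift linked to arm can look like a treatment effect.
- **Symptoms.** SCAT-5 symptom number and severity are secondary endpoints, rated at every draw in an open trial. A self-rating made under a cap with coolant at 0 °C is not the same measurement as one made without it.

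**Working it through.** No sample size, power or error rate is involved, so there is no figure of the plan's to reproduce. The check is a timeline in minutes after the end of the fight.

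**Inputs**
- s = time of the initial post-fight sample; c = start of cooling.
- s ≤ c, because the Abstract puts the draw and symptom rating before cooling.
- c ≤ 10 and duration ≥ 45, from Procedures and Measurements.

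**Formulas**
- Earliest end of cooling = c + 45.
- Fight clock: sample at 45, cooling completed 45 − c, still to run c.
- Initial-sample clock: sample at s + 45, still to run (c + 45) − (s + 45) = c − s.
- Difference between the two clocks = s.

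**Results at the minimum duration**

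| c | Earliest end | Fight clock: completed of 45 | Fight clock: still to run | Initial-sample clock, s = c/2: sample at | Still to run |
|---|---|---|---|---|---|
| 2 | 47 | 43 | 2 | 46 | 1 |
| 5 | 50 | 40 | 5 | 47.5 | 2.5 |
| 10 | 55 | 35 | 10 | 50 | 5 |

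**Fight clock.** Cooling is complete at minute 45 only if c = 0, which the preceding draw and symptom rating rule out. The completed share runs from 35/45 = 78% to just under 100%.

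**Initial-sample clock.** Since c ≥ s, the remainder c − s is never negative. It is zero only if the cap goes on at the moment of the draw and cooling lasts exactly 45 minutes; otherwise it is positive, up to 10 minutes. The sample can coincide with the end of cooling but cannot follow it.

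**If staff wait for cooling to end** while controls are drawn at minute 45, the gap between arms is (c + 45) − 45 = c. That is up to 10 minutes, or at most 10/45 = 22% of the nominal interval, at the minimum duration, and more if cooling runs longer.

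**Difference between clocks.** In the cooled arm, s lies between 0 and 10 minutes. The article sets no limit on s for controls beyond saying that the sample is immediate.

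**The case against.** The strongest reply is that this is loose labelling in a condensed article. The Abstract may give the true rule, with 45 minutes post fight only a visit name. If the cap goes on straight after the draw, the shortfall is perhaps a few minutes. Figures 1 and 2 are not available here and might settle the origin. This narrows the likely size but does not remove the conflict: the written passages still disagree, and even under the Abstract's clock the sample cannot come after cooling.

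A reader might infer that the arms are in fact sampled at different times, or that cooled boxers are in fact assessed mid-treatment. The documents do not say so. They set one nominal time for both groups, and the order in Procedures and Measurements intends assessment after cooling. Unequal or mid-treatment sampling is a foreseeable result of the conflict, not a prescribed one.

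A reader might also take 10 minutes as the least shift for the cooled arm. It is the least only for a boxer who starts at minute 10; for the arm it is an upper limit at the minimum duration.

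Two further points stand. The Abstract's primary contrast is immediate post fight against day 6, and its list of primary markers omits S100B. The Adverse Events section says that deviations in sample time and cooling duration will be noted, so some times may be recoverable. However, a deviation cannot be identified consistently while the nominal time is itself in conflict.

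**Conclusion.** The conflict is real and rests on the text and simple arithmetic. There are two time origins, and the stated order of cooling then sampling cannot be met under either. At minute 45 post fight, cooled boxers have completed 35 to just under 45 of the minimum 45 minutes. If only the cooled arm waits, it is sampled up to about 10 minutes later than controls, and later still if cooling exceeds the minimum.

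The consequence is confined to the 45-minute biomarker comparison, S100B above all, and the 45-minute SCAT-5 secondary outcome. It would be tempting to conclude that the primary endpoint is compromised. The Abstract's definition does not support that; the sample could enter the primary endpoint only under the looser Trial Design wording of changes over the first 6 days.

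The size of any bias cannot be derived, since the documents give no rate of change for S100B and no actual sampling times. The conclusion assumes that the Abstract's order of draw, rating and cooling is followed in practice.

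**What to change.** 1. Reconcile the Abstract, Procedures and Measurements, the sampling list after Figure 3, Table 1 and Data Collection on one time origin. Reconcile the statements on cooling start, cooling duration and sample time with one another. The cooling rule itself is not for this review to set.
2. For boxers still to be enrolled, set one nominal sampling time, the same in both arms, that falls after cap removal.
3. Record clock times for fight end, each sample, cap on and cap off, building on the deviation log already planned under Adverse Events.
4. For boxers already sampled, report actual sampling times by arm and whether the cap was on. Treat the 45-minute arm comparison as descriptive, or show it in a sensitivity analysis restricted to overlapping sampling times. Adjust for actual time only where times overlap between arms: if only cooled boxers waited, time would be nearly collinear with arm, and adjustment could remove or destabilise the arm effect.

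**Cost.** A few minutes' wait for controls, and a change of nominal time late in recruitment. With 41 boxers included of a planned 40–50, the change creates a second timing regime for the few who remain, and this should be stated in the report. The wording changes and the reporting of actual times cost little.

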**Figure 1 figure1:**
[figure not shown]
Boxers that participate in direct final bouts or single-fight events will only engage in one boxing bout. SCAT-5: Sports Concussion Assessment Tool-5.

**Figure 2 figure2:**
[figure not shown]
Boxers who participate in tournaments can either fight one or two boxing bouts, depends on whether they win or lose. SCAT-5: Sports Concussion Assessment Tool-5.

The PolarCap System consists of a portable cooling system, designed to reduce brain temperature by controlled cooling of the scalp and neck with a circulating coolant (PolarCap Coolant, PolarCool AB). The coolant is maintained at 0 °C and flows through a silicone-based head cap. An insulating neoprene cover is put on top of the cap for isolation. The players are allowed to relax (sitting or supine) as long as the cooling head cap and neoprene cover remain in place on the head [22] Should the boxer experience discomfort and wish to discontinue the intervention, the cap is removed and the athlete is excluded from the study. All boxers follow the return-to-fight protocol. The standardized protocol is to return to physical exercise during the first 6 postfight days. During this time, the boxer may do all forms of physical exercise except sparring, match fight, or other activities resulting in impacts to the head or body (Figure 3).

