### Allocation

After all boxers have approved participation in the study during the tournament, and signed the informed consent, the study staff makes an allocation on paper slips that equals the number of participants. Then the boxers randomly, by drawing a paper slip, receive either a sign for receiving head-and-neck cooling (C=cooling) or NC (no cooling; Figures 1-2). All allocations are finalized a minimum of 3 hours before the start of the tournaments.

The enrollment of participants will be done by a researcher ([name]) aided by boxing coaches.

After the boxing bout, and after the boxer is evaluated for red flags mandating transport to the nearest hospital, the boxer is brought to the intervention station to apply the PolarCap system as previously described.

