### Adverse Events

Any adverse events reported by the participant during the study period are noted and reported. Specifically, any deviation from the protocol (eg, sample time point, duration of head-and-neck cooling) will be noted. Symptoms, such as headache, nausea, and dizziness, are reported to the medical doctor and study researcher ([name]), although these symptoms may also be caused by the SRC per se [15]. No adverse events are expected, based on our previous study where 61 elite ice hockey players were cooled without any reported adverse events [15].

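### A cooled boxer who stops cooling for discomfort is excluded from the study: a post-randomisation exclusion possible in one arm only, which can bias the comparison and loses follow-up data

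*Protocol article*

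**What the plan says.** **The rule.** In the description of the cooling system (Procedures and Measurements, text after Figure 2): "Should the boxer experience discomfort and wish to discontinue the intervention, the cap is removed and the athlete is excluded from the study".

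**Timing of randomisation.** The Abstract (Methods) states: "Boxers are randomized to intervention or control management by 1:1 allocation before baseline testing". The Allocation section adds: "All allocations are finalized a minimum of 3 hours before the start of the tournaments". Cooling is given only after the boxer's last bout.

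**What each arm receives.** After the first postfight sample, "the boxers receive either acute selective head-and-neck cooling for 45 minutes or routine postfight management". The trial is "designed as a randomized, controlled, open, single-center superiority trial with 2 parallel groups".

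**Safety and deviations.** One secondary objective is "To determine any adverse event associated with the head-and-neck cooling". The Adverse Events section says that "any deviation from the protocol (eg, sample time point, duration of head-and-neck cooling) will be noted", and that adverse events reported by participants are recorded. It also observes that headache, nausea and dizziness may stem from the concussion itself.

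**Follow-up.** The sampling schedule under Procedures and Measurements applies the day 3 and day 6 draws to every boxer, with no exception for those who stop cooling.

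**A related item.** The exclusion criteria include "Participation in competitive fights, match-sparring, or any training causing additional head impacts during the 6-day postfight follow-up period after being included in the study".

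**The concern.** A control boxer has no cap to take off, so only the cooled arm can lose boxers through this rule. The loss is determined after allocation, by something that may be related to outcome. If boxers with more postfight symptoms find the cap harder to bear, and those boxers also differ in biomarker course or SCAT-5 scores, the cooled boxers who remain are a selected group set against an unselected control group. Randomisation no longer protects the comparison.

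A later analysis plan cannot fully repair this. If excluded boxers are not sampled on day 3 and day 6, the data for an as-randomised analysis of the day 6 endpoint do not exist.

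The article is also inconsistent. One section makes stopping cooling a ground for exclusion. Another treats a departure from the planned cooling duration as a deviation to be noted. A third takes samples from every boxer on days 3 and 6. These passages must be reconciled.

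**Working it through.** **Step 1: is the exclusion post-randomisation and one-armed?** Allocation is final at least 3 hours before the tournament, and cooling follows the last bout, so any stop comes after allocation. Controls receive routine management without a cap. The answer is yes on both counts.

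**Step 2: can it be related to outcome?** The Adverse Events section names symptoms to report and says the injury itself may cause them. A link between discomfort and outcome is therefore plausible on the article's own account. Its strength is not stated.

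**Step 3: the plan's own figures.** The article gives no stopping rate, so there is no planned figure for this loss to reproduce. Sample Size and Statistical Power gives 20 per group for power 0.8, raised to 25. The step is 20/(1 − 0.20) = 25, so a 20% loss is implied and correctly inflated. The 20 itself cannot be confirmed, because the readable text gives no SD and no alpha.

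For scale, 20 per group at two-sided 0.05 (assumed) and power 0.8 detects about 0.91 SD with a t-test. By the normal approximation it is (1.960 + 0.842) × √(2/20) = 0.886 SD, so a 20% difference implies an SD of 20/0.886 = 22.6%.

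**Step 4: possible shift, by simulation.** Inputs from the article: 20 controls and 21 cooled (Abstract, Results). Assumptions: a standard normal outcome with higher values worse, no true effect, a two-sided 0.05 t-test, and k cooled boxers with the highest discomfort score removed, where that score has correlation ρ with outcome. The expected shift is

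shift = −ρ × (sum of the k largest expected order statistics of 21) / (21 − k).

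The three largest are about 1.89, 1.43 and 1.16.

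- k = 2, ρ = 1: −(1.89 + 1.43)/19 = −0.17; simulated −0.18.
- k = 3, ρ = 1: −(1.89 + 1.43 + 1.16)/18 = −0.25.

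| Stoppers k | ρ | Shift (SD) | Type I error |
|---|---|---|---|
| 1 | 0.5 | 0.05 | about 5.5% |
| 2 | 0.3 | 0.05 | 5.4% |
| 3 | 0.3 | 0.07 | about 5.7% |
| 2 | 0.5 | 0.09 | about 6% |
| 3 | 0.5 | 0.12 | about 7% |
| 2 | 1 | 0.18 | 10% |
| 3 | 1 | 0.25 | 14% |

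At ρ = 0 there is no bias. In this model the excess error falls on the side favouring cooling: at ρ = 0.5, false claims of benefit rise from a nominal 2.5% to 4.8% (k = 2) and 6.0% (k = 3).

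**Step 5: a second route, at the planned 25 per arm.** The shift equals the excluded fraction times the gap between excluded and retained boxers.

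- 2 of 25, gap 0.5 to 1 SD: 0.08 × 0.5 = 0.04 to 0.08 × 1 = 0.08 SD; type I error 5.2 to 5.9%.
- 5 of 25, same gap: 0.20 × 0.5 = 0.10 to 0.20 × 1 = 0.20 SD; type I error 6.3 to 10.2%.

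The two routes agree: the effect is small with few stoppers or a weak link, and material when several stop and the link is strong.

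**The case against.** The strongest reply is that stops are likely to be rare and the study modest in its claims. The article reports 61 cooled ice hockey players with no adverse events, its Results text describes no boxer who left because of the cap, and the Discussion calls the study explorative. This stands as an argument about size. It does not make the rule sound, and the participant flow figure is not available to show whether any stop has occurred.

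A reader might infer several stronger things that the article does not support:

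- **That tolerability failures vanish from the safety results.** Adverse events and deviations in cooling duration are to be noted, so a stop may well be recorded when it happens. What is lost is later follow-up and an assured place in the denominator.
- **That samples already drawn are thrown away.** No section says so. It is only one reading of being excluded.
- **That the control arm loses nobody.** This is true of the cap rule only. Voluntary withdrawal, an opponent dropping out and the head-impact item can affect either arm.
- **That the bias must favour cooling.** The primary endpoint is a change from the immediate postfight sample to day 6. Boxers with high postfight values could show the largest falls, and removing them could work against cooling.
- **That type I error is 10 to 14%.** This needs discomfort to rank outcome perfectly and 2 or 3 of 21 boxers to stop.
- **That the boxer who withdrew with nausea and vomiting was a cooling stop.** He left after the bout and before further testing, and nothing links this to the cap.

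**Conclusion.** The point holds in limited form. As written, the rule is a post-randomisation exclusion that only the cooled arm can meet, and nothing in the article keeps these boxers in follow-up or in the analysis. It can bias the comparison, and it conflicts with the sections on deviations and sampling.

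Its size and direction are unknown, because neither the number of stoppers nor their difference from other boxers is given. Under a moderate assumption (2 to 3 stoppers, correlation 0.5), the shift is about 0.09 to 0.12 SD against a detectable difference of about 0.91 SD, with type I error about 6 to 7%. The range runs from no bias to an upper bound of 0.25 SD and 14% for up to three stoppers.

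The head-impact item is a secondary and weaker point. Behaviour in the 6 days after inclusion cannot be assessed at enrolment, so this is also a post-randomisation exclusion, but one that can apply in both arms. That it would follow allocation in an open trial is possible but not shown.

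**What to change.** Leave cap removal at the boxer's wish unchanged. Replace the clause that excludes the athlete with wording to this effect: the boxer stays in the trial unless he or she withdraws consent; later SCAT-5 ratings and blood samples are taken if the boxer agrees; cooling minutes and the reason for stopping are recorded, and the stop is counted as a tolerability outcome; the boxer is analysed in the allocated arm. A per-protocol analysis can be secondary. For boxers who have already stopped, report them by arm and include the samples held. Reconcile this wording with Adverse Events and the sampling schedule.

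Take the head-impact item out of the exclusion criteria and record it as a post-randomisation event. Keep the samples taken before it, and handle later ones in a sensitivity analysis.

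**Cost.** Protocol wording and a few day 3 and day 6 visits. Follow-up already missed cannot be recovered. The target of 25 per group can stand, although keeping stoppers may dilute the effect. With SD 22.6%, two-sided 0.05, all 25 per group analysed and no effect in stoppers (all assumed), 2 of 25 stopping reduces a 20-point effect to 20 × 23/25 = 18.4 (power about 0.82). With 5 of 25 it falls to 16 (power about 0.71).
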